**WS3 phase 2: Staff experience on implementation**

Phase 2 will focus on understanding nursing home staff experiences of implementing the intervention and their perceived impact of the educational intervention on their practice and resident care. Focus groups (*n* = 4) will be conducted with up to 32 nursing home staff, including managers and nurses. Depending on data saturation, participant numbers may be adjusted. Recruitment will follow the completion of the post-test questionnaires in phase 1, with participants offered the opportunity to join the focus groups.

Table 1 provides an overview of workstreams and phases for this study.

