**WS3 phase 1: Nursing home staff knowledge, self-efficacy, and usability**

In phase 1, nursing home staff knowledge and self-efficacy in providing care for residents with diabetes will be assessed before and after implementing the digital intervention via a pre- and post-test questionnaire. The questionnaire, delivered electronically through the intervention, will include the Michigan Diabetes Knowledge Test (DKT2) (twenty-three items) [42] and an eight-item questionnaire on self-efficacy in providing care to residents with diabetes. The Michigan Diabetes Knowledge Test (DKT2) is a widely validated tool used to assess general diabetes knowledge and has demonstrated good internal consistency (Cronbach’s alpha = 0.77) [42]. The self-efficacy questionnaire was adapted from established scales used in similar care settings, with items reviewed by experts during the co-design process to ensure face validity. Approximately 100 registered nurses will be recruited from ten nursing homes across Northern Ireland. These homes will represent both rural and urban settings. A power calculation will not be required as we plan to conduct proximal testing as per NIHR guidelines on complex interventions [27]. However, the anticipated sample of approximately 100 registered nurses from 10 nursing homes is consistent with recommendations for feasibility and proximal outcome testing in complex intervention research [27]. This sample size allows for preliminary evaluation of changes in knowledge and self-efficacy, while also accounting for expected attrition in this population. Analytics, such as user engagement and time spent on the platform, will also be analysed to evaluate the intervention’s usability. Usability will be further evaluated using the 31-item User Engagement Scale (UES) questionnaire [43], which will address the ‘practicality’ aspect of the testing. The User Engagement Scale (UES) has robust psychometric properties, including strong reliability and construct validity in digital health education contexts [43]. The selection of these tools was guided by their proven validity, relevance to the target population, and alignment with the intervention’s educational objectives.

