#### 2.2.3. Framework

The Consolidated Framework for Implementation Research (CFIR) will be used to systematically guide the evaluation of the digital diabetes education intervention within nursing homes. Specifically, CFIR’s five domains, (1) intervention characteristics, (2) outer setting, (3) inner setting, (4) characteristics of individuals, and (5) implementation process, will inform the development of data collection tools and the analysis of both qualitative and quantitative findings in Workstream 3 [45,46]. For example, interview and focus group questions will be mapped to CFIR constructs to explore how factors such as organisational culture, staff readiness, and external policy influence the adoption and integration of the intervention. This approach will ensure that the evaluation captures key contextual and process-related determinants of successful implementation, enabling identification of barriers and facilitators unique to the nursing home environment [45,46]. Data generated is likely to inform recommendations for scaling and sustaining digital education interventions in similar care settings.

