The outcomes of this study are proximal in nature and focus on the extent to which the intervention impacts knowledge, self-efficacy, acceptability, care practice, and short-term resident outcomes. While initial findings may be promising, expectations should remain cautious and grounded in the early-stage nature of this work. Larger, randomised studies will be required to validate these effects and determine long-term impacts. Should these outcomes be positive, further testing could test medium- and longer-term outcomes which may lead to sustained improvements. Furthermore, if the intervention proves successful, it holds the potential for scalability at both national and international levels. This scalability could be achieved through partnerships with healthcare organisations and policymakers who recognise the importance of quality diabetes care in long-term care settings. Given the high staff turnover in healthcare [52,53,54], adopting a digital approach for training presents a more affordable and sustainable solution compared to traditional face-to-face methods [55]. Digital platforms offer flexibility [41,56], allowing training to be standardised and readily accessible to new staff as they onboard.

There are methodological limitations within this study protocol that should also be acknowledged. The study does not use randomisation, which may introduce selection bias. Furthermore, the follow-up period is relatively short and may not capture sustained behavioural changes or long-term impacts on resident outcomes. The participant sample may also lack diversity in terms of geographical and cultural representation. These limitations should be considered when interpreting the findings and their generalizability.

It is anticipated that the intervention developed during this study will not only impact care provision for residents with diabetes in nursing homes but, if successful, could also have scalability at both a national and international level in the future. However, practical challenges such as the need for staff training in digital literacy, inconsistent access to devices and internet connectivity, and potential resistance to change within organisational cultures must be considered. Addressing these barriers will be key to the intervention’s wider adoption and long-term success.

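### The only described route into the WS3 focus groups is an offer to phase 1 nurses after an in-platform post-test, so disengaged staff are unlikely to be invited, and managers not enrolled as nurses have no stated route

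*Protocol article*

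**What the plan says.** All of the following is in the protocol article.

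- **Source sample (WS3 phase 1).** "Approximately 100 registered nurses will be recruited from ten nursing homes across Northern Ireland". The sample size is described as adequate for a preliminary evaluation "while also accounting for expected attrition in this population". No attrition rate is given.
- **Delivery of the pre- and post-test (WS3 phase 1).** "The questionnaire, delivered electronically through the intervention" covers both the knowledge test and the self-efficacy items.
- **Purpose of the focus groups (WS3 phase 2).** "Phase 2 will focus on understanding nursing home staff experiences of implementing the intervention", together with the perceived effect on practice and resident care.
- **Size and make-up (WS3 phase 2).** Four groups "will be conducted with up to 32 nursing home staff, including managers and nurses".
- **Route in (WS3 phase 2).** "Recruitment will follow the completion of the post-test questionnaires in phase 1, with participants offered the opportunity to join the focus groups". No other route is described.
- **Use of the findings (section 2.2.3, Framework).** Focus group questions are mapped to CFIR constructs, "enabling identification of barriers and facilitators unique to the nursing home environment", and the data are expected to inform advice on scaling.
- **Obstacles the authors foresee (section 3, Discussion).** Digital literacy needs, "inconsistent access to devices and internet connectivity, and potential resistance to change within organisational cultures".

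**The concern.** A study of implementation barriers needs to hear from people who met them. Here the offer comes after a questionnaire that sits inside the product being evaluated. Someone who could not log in, had no device, lost interest or gave up is less likely to reach that questionnaire, and so less likely to receive the offer. The focus groups would then lean towards staff for whom the platform worked.

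The quantitative strand has the same lean. The paired t-tests in section 2.2.2 need a measurement before and after, so they too rest on those who completed the post-test. If the focus groups come largely from the same people, agreement between the two strands is weak corroboration. The advice on scaling would rest on that agreement.

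The second issue is a mismatch between adjacent sections. Phase 2 counts on managers, while the sample it draws from is described as registered nurses. Managers are well placed to speak about the organisational setting, which is one of the CFIR domains, so how they enter should not be left to inference.

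**Working it through.** There is no stated figure to reproduce, and no power or error-rate formula applies. The question is who can be reached by the recruitment route, so the check sets the sections side by side and adds simple counts.

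**Step 1: trace the route.** Enrolment in phase 1 as a registered nurse → use of the platform → post-test through the platform → offer of a focus group place. WS3 phase 2 gives no branch for anyone who drops out before the post-test.

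**Step 2: look for another source on disengagement within WS3.** Platform analytics (WS3 phase 1 and section 2.2.2) are summarised descriptively. They can show that use was low, but not why. The User Engagement Scale is a questionnaire for users. The limitations in section 3 cover non-randomisation, short follow-up and limited geographical and cultural diversity, but not this selection. The focus groups are therefore the only described WS3 component that could give reasons for stopping.

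**Step 3: check the managers.** WS1 phase 2 lists home managers and registered nurses as separate eligible roles. The same section draws its interviewees, managers included, from a network described as over 400 registered nurses. So a manager may be a registered nurse and may be in phase 1, but need not be. For those who are not, no route is stated.

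**Step 4: counts from the documents.** Four groups and up to 32 people give 32 / 4 = 8 per group. Against about 100 nurses, 32 / 100 = 32%.

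**Step 5: illustration only.** The attrition range of 10% to 40% is an assumption.

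| Assumed attrition | Completers of 100 | Non-completers | 32 places as share of completers | Non-completers expected among 32 if all 100 are invited and accept equally |
|---|---|---|---|---|
| 10% | 90 | 10 | 32 / 90 = 36% | 32 × 0.10 = 3.2 |
| 40% | 60 | 40 | 32 / 60 = 53% | 32 × 0.40 = 12.8 |

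If the offer reached completers alone, the last column would be zero. So, under these assumptions, the stake is about 3 to 13 of the 32 places. This shows how many non-completers would go unheard. It does not measure bias in the findings.

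**The case against.** The strongest reply is that the text sets no eligibility rule. Saying that recruitment comes after the post-test can be a statement about timing, and the people offered a place could be everyone enrolled in phase 1. This stands. A reader might infer that only completers are eligible and that non-completers are formally excluded, but the document does not say so. It does not follow that the procedure is sound: on the timing reading too, nothing ensures that someone who left the platform is contacted.

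Second, a reader might infer that no manager is in the pool. That is too strong, for the reason in step 3. What remains is a mismatch to reconcile.

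Third, nothing in the document ties the obstacles in section 3 to missing the post-test. Turnover, leave or workload could also explain it. Completers and managers can describe device, connectivity and cultural problems in their home, including those of colleagues, so it cannot be stated as fact that barriers will be under-reported. This stands as a limit on how firmly the consequence can be put. Second-hand accounts are still a weaker source than those of the staff concerned.

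Fourth, this is a condensed article, and invitation lists are often left to a fuller protocol. That would answer a complaint about missing detail. Here, however, the article states a procedure, and it is the stated procedure that produces the tilt.

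Finally, any percentage excluded depends on an attrition rate that the document does not give. This also stands.

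**Conclusion.** The point holds in a limited form and is worth a cheap correction. As written, the one described path into the focus groups runs through phase 1 registered nurses after a post-test housed in the platform. Following it would tilt the groups towards engaged users, while the strand is meant to find barriers and no other part of WS3 records why staff stopped. WS3 phases 1 and 2 also need to be reconciled on managers.

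The direction of the tilt is predictable, but its size is not known. The conclusion rests on two readings: that the offer is made at or after the post-test to those still reachable through the platform, and that some of the expected attrition consists of staff who stopped using it. The document does not support a claim that non-completers are barred, that managers are absent, or that a particular share of users is shut out.

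**What to change.** Amend the recruitment sentence in WS3 phase 2 along these lines:

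1. All staff given access to the intervention are invited to the focus groups whether or not they completed the post-test, by a channel outside the platform such as email.
2. Where platform analytics can be linked to individuals, they are used to seek some low and non-users within the same four groups and 32 places. If they cannot be linked, the open invitation in item 1 still applies. A fixed quota or a separate manager group would be a matter of preference and is not needed to meet this point.
3. The managers of the ten homes are invited directly, so that the descriptions of the sample in WS3 phases 1 and 2 agree.

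The cost is a changed invitation list and some extra follow-up, with no additional groups or places. Low users may be harder to recruit. Because section 2.2.1 has the focus groups run online through Microsoft Teams, staff without devices or connectivity may still be missed. That remaining gap should be reported as a limitation alongside those in section 3. The change has to be made before WS3 recruitment starts, since the selection cannot be repaired afterwards.

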### 2.2. Data Analysis

#### 2.2.1. Qualitative Analysis

Qualitative data will be collected through one-on-one interviews (Workstream 1; WS1) and focus groups (Workstream 3; WS3), both conducted online via Microsoft Teams to enhance participant accessibility and scheduling flexibility. All sessions will be audio recorded in full. The recordings from WS1 and WS3 will be transcribed verbatim and imported into NVivo version 11 for data management and analysis. A thematic analysis approach, as described by Braun and Clarke [44], will be employed to systematically identify, analyse, and report patterns (themes) within the data. One researcher will conduct all individual interviews, while two researchers will co-facilitate each focus group. All researchers involved in the qualitative data collection will have prior training and experience in the respective qualitative methodologies employed.

#### 2.2.2. Quantitative Analysis

Quantitative data will be analysed using IBM SPSS Statistics, version 26. Descriptive statistics will be used to summarise findings from the modified Delphi study (WS1) as well as platform-generated internal analytics collected during the evaluation phase (WS3). These analytics include metrics such as the duration of time care staff engage with the digital intervention. To evaluate changes in nursing home staff knowledge and self-efficacy following exposure to the intervention, dependent (paired samples) *t*-tests will be conducted as part of WS3. This analysis will provide a preliminary indication of the intervention’s potential effectiveness.

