#### 2.2.4. Ethics and Governance

This study has received ethical approval from the Faculty of Medicine and Health Sciences at Queen’s University Belfast (MHLS 24_167). Local governance will be managed by each nursing home or nursing home group, as these organisations operate independently of the National Health Service (NHS) in Northern Ireland. Microsoft Teams, which complies fully with the Data Protection Act [47], will be used for data management and has the capability to record meetings, ensuring thorough capture of all participants’ views. Video recordings will be securely stored and deleted following transcription. Informed consent will be collected from all participants, and their involvement will be kept confidential. Participant information will be accessible only to the research team, and participants’ identities will be anonymised in all publications and study outputs. The study will be conducted in accordance with the Declaration of Helsinki [48]. All data will be stored on password-protected computers at Queen’s University Belfast and anonymised transcription files on a secure Microsoft Teams site accessible only to the research team. All data will comply with the Data Protection Act [47] and be retained for 5 years post-study before being destroyed.

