## 3. Discussion

There is a significant gap in research focused on the development and testing of digital interventions aimed at improving care staff understanding of diabetes management and symptom monitoring in nursing homes. As the prevalence of diabetes continues to rise, particularly among older adults, the need for effective training and support for care staff has never been more critical [49]. A systematic review of 63 interventional studies designed to change care staff practices in nursing homes revealed that while achieving change is feasible, the process is inherently complex [50]. This complexity is influenced by various factors, including staff attitudes, existing knowledge levels, and the organisational culture within nursing homes. Compared to similar digital educational interventions in long-term care, this study is distinguished by its co-design methodology involving diverse stakeholders including residents, carers, and frontline staff. While other studies have focused on clinical or face-to-face training formats, few have integrated participatory design into digital diabetes education in nursing home settings, highlighting the innovation and originality of this approach. This study aims to actively engage end users through a multi-faceted approach, including one-on-one interviews, a Delphi study, a co-design group, and focus groups. This inclusive methodology not only ensures that the voices of care staff are heard but also fosters a sense of ownership and commitment to the intervention being developed [25,51].

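### The paired t-tests make no allowance for about 100 nurses being grouped in ten homes; if changes correlate within homes, the standard errors are too small

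*Protocol article*

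**What the plan says.** The evaluation sample is described under WS3 phase 1: "Approximately 100 registered nurses will be recruited from ten nursing homes across Northern Ireland". That averages ten nurses per home. No sample-size calculation is offered: "A power calculation will not be required as we plan to conduct proximal testing as per NIHR guidelines on complex interventions". The same paragraph says that the sample suits its purpose "while also accounting for expected attrition in this population", without giving a rate.

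Section 2.2.2 (Quantitative Analysis) names one inferential method, in the sentence beginning "To evaluate changes in nursing home staff knowledge and self-efficacy following exposure to the intervention, dependent (paired samples" and ending with t-tests. Its purpose is modest: "This analysis will provide a preliminary indication of the intervention’s potential effectiveness". No home term, mixed model or cluster-robust variance appears anywhere in the article. No significance level, confidence interval or intra-home correlation is stated either.

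Elsewhere the home is treated as something that matters:
- The Discussion, commenting on a cited review of interventions to change staff practice, says such change is complex because of factors "including staff attitudes, existing knowledge levels, and the organisational culture within nursing homes".
- Section 2.2.3 (Framework) says that organisational culture and the readiness of staff will be explored as influences on uptake, and applies the framework to the quantitative as well as the qualitative results.
- The Discussion also lists uneven access to devices and the internet, and cultural resistance to change, as practical obstacles.
- On governance, section 2.2.4 says: "Local governance will be managed by each nursing home or nursing home group".

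**The concern.** A paired t-test is a one-sample t-test on individual change scores. The pairing deals with the two measurements on one nurse. It does not deal with nurses who share a home, because it takes every change score as independent of every other. If some homes respond better than others, nurses in one home carry partly the same information. The standard error of the mean change is then understated, p-values are too small, and any interval built on that standard error is too short. This applies to both knowledge and self-efficacy.

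This is more than a detail left to a later plan. The article names the test, so an analysis plan that allowed for home would have to replace it. There is no control group and no power calculation, so the mean change and its uncertainty are the main quantitative result of the evaluation. The Discussion makes further testing depend on positive outcomes.

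**Working it through.** **Is there a figure to reproduce?** No. The protocol gives about 100 nurses and ten homes, but no alpha, SD, effect size, power or ICC.

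**Inputs**
- From WS3 phase 1: k = 10 homes and about 100 nurses, so m = 10 per home if the homes are equal in size.
- Assumed: a nominal two-sided 5% level; an ICC of change, ρ, between 0 and 0.10; for attrition, m = 7 per home (30% loss).

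**Which ICC matters.** Write a nurse's score as a home effect plus an individual part, before and after. A home effect that is the same at both times drops out of the difference. What remains is between-home variation in the *change*. The ICC of raw scores would therefore overstate the problem if home differences are mostly stable.

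**Formulas**
- Design effect: DE = 1 + (m − 1)ρ
- True standard error divided by the paired-test value: √DE
- Effective sample: km / DE
- Actual error of a nominal 5% test: 2[1 − Φ(1.96/√DE)]

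For ρ = 0.05: DE = 1 + 9 × 0.05 = 1.45; √1.45 = 1.20; 100/1.45 = 69; 1.96/1.204 = 1.63, which gives an error of 10.4%.

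| ICC of change (assumed) | DE | SE ratio | Effective n | Error, formula | Error, simulated paired t | Error, simulated t on home means |
|---|---|---|---|---|---|---|
| 0 | 1.00 | 1.00 | 100 | 5.0% | 5.1% | 5.2% |
| 0.01 | 1.09 | 1.04 | 92 | 6.0% | 5.9% | 4.8% |
| 0.02 | 1.18 | 1.09 | 85 | 7.1% | 7.2% | 5.1% |
| 0.05 | 1.45 | 1.20 | 69 | 10.4% | 10.2% | 5.0% |
| 0.10 | 1.90 | 1.38 | 53 | 15.5% | 15.6% | 5.0% |

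The simulations used 40,000 runs per row, with normal change scores and equal home sizes. Formula and simulation agree within 0.3 percentage points. The t-test on ten home means stays close to 5% throughout.

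**Attrition.** With m = 7, ρ = 0.05 gives DE = 1 + 6 × 0.05 = 1.30 and an error of 8.6%; ρ = 0.10 gives DE = 1.60 and 12.1%. The excess is smaller because each home contributes fewer nurses.

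**Interval width, in SDs of change, 10 × 10.** The paired t-test gives 1.984 × 1/√100 = 0.198. The home-mean analysis (9 df) gives 2.262 × √(DE/100): 0.226 at ρ = 0, 0.272 at 0.05 and 0.312 at 0.10. At ρ = 0 the ratio is 0.226/0.198 = 1.14, so 14% of extra width comes purely from moving from 99 to 9 degrees of freedom. At 0.05 the total widening is 0.272/0.198 = 1.37, of which clustering alone accounts for a factor of 1.20.

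**The case against.** The best defence is that the correlation is not established. If the ICC of change is zero, the paired t-test is valid, and at 0.01 the error is only about 6%. The materials are digital, and the protocol describes staff access over 12 weeks, not teaching in groups by home. The remark on organisational culture concerns care practice, whereas the tests are on a knowledge score and a self-efficacy scale. The result is called preliminary, the Discussion asks for caution and for larger randomised studies, and no decision rule hangs on a p-value.

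Much of this stands, and it rules out several stronger readings that a reader might infer:
- *That the protocol breaks its own 5% error rate.* It states none; 5% is a conventional level assumed here.
- *That the intervals are certainly too narrow.* The protocol plans no stated interval and gives no ICC. Its remarks make correlated change likely, not certain.
- *That roll-out is by home.* The protocol does not describe one.
- *That all the widening in a home-level analysis is caused by clustering.* Part is the price of fewer degrees of freedom, as shown above.

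What the defence does not answer is that the named test assumes the home is irrelevant to change, while the evaluation framework sets out to study how the home setting shapes uptake. A preliminary label lowers the stakes but does not make a standard error correct.

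**Conclusion.** The point holds in conditional form. The protocol fixes an analysis that ignores home, in a design with ten homes and about ten nurses in each, and gives its own reasons to expect homes to respond differently. For an ICC of change from 0 to 0.10, the true standard error is 1.00 to 1.38 times the paired-test value, and a nominal 5% test has an error between about 5% and 16%; attrition reduces the excess. These sizes rest on an assumed ICC range, an assumed 5% level and equal home sizes. Severity is should-fix: the remedy is cheap and the defect lies in the named method, but the result is offered only as a preliminary indication.

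**What to change.** Record the nursing home on each pre and post questionnaire; the protocol does not say that this is done. Then replace the paired t-test sentence in section 2.2.2 with one of these:

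- a linear mixed model on individual change scores, with a random intercept for home and Satterthwaite degrees of freedom; or
- a one-sample t-test on the ten home-mean changes, with 9 degrees of freedom.

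If raw pre and post scores are modelled instead, include a random home-by-time effect, because a plain home intercept cancels out of the within-nurse change and would leave the problem in place. For each outcome, report the mean change with a 95% confidence interval and the ICC of change, which would also help to plan the larger studies that the Discussion calls for.

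The cost is one sentence and one recorded field, with no extra participants, and the planned software can fit either option. The statistical price should be stated openly: intervals will be wider (about 14% wider for the 9-df option even if the ICC is zero), and ten homes give only an imprecise estimate of between-home variance.
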